### Outcomes

#### Clinical effectiveness

##### Primary outcome

Multiple Sclerosis Quality of Life (MSQOL-54). MSQOL-54 is a multidimensional measure of health-related quality of life that combines both generic and MS-specific items in a single instrument [48, 49]. This 54-item instrument generates 12 subscales along with two summary scores, and two additional single-item measures. The subscales are: physical functioning, role limitations-physical, role limitations-emotional, pain, emotional well-being, energy, health perceptions, social functioning, cognitive functioning, health distress, overall quality of life, and sexual functioning. The summary scores are physical health summary and mental health summary. The single item measures are satisfaction with sexual function and change in health.

The primary time point at which the effectiveness of MPVC is determined is 2 years.

#### Cost evaluation outcomes

Total costs over a 2-year period will be estimated using a bottom-up (or micro-costing) approach, where information on each element of service used is multiplied by an appropriate unit cost and summed to provide an overall total cost [50]. The time horizon will be the same as the follow-up period of the main study: from baseline and then every 3 months until a total period of 2 years.

We will assess intervention costs, healthcare costs, patient and family costs, and costs outside the health care sector. For this study, we will develop a cost questionnaire specially designed for this group, based on existing questionnaires [51] which will measure all relevant costs aspects.

To measure the actual use of resources, data will be obtained using combined sources (registrations by professionals and cost questionnaire). Resources used related to the interventions will be based on the registered time all professionals spent on the treatment. Intervention costs will include all the costs that will contribute to the development and administration of the MPVC and CAU, for example costs of training and travel expenses. All use of resources by the patient and their family in and outside the health care sector will be measured by means of a cost questionnaire (EQ-5D-5L), in which they continuously record volumes of resource utilization during the follow-up period.

Costs will be calculated by multiplying volumes (resource use) with unit costs. For units costs we will used the Dutch cost guidelines [6, 52, 53]. Productivity costs will be calculated by means of the friction cost method, based on a the mean added value of the Dutch working population. The friction costs method takes into account production losses confined to the period needed to replace a sick employee. In case of uncertainty, we will use a conservative estimation (i.e. the lowest cost price). Cost prices will be expressed in 2022 Euro. If necessary, existing cost prices will be updated to 2022 using the consumer price index. Resource use measurement (costs) will be measured continuously (for details see cost measurement), outcomes for the economic evaluation study will be measured at pre-test before randomization to the two study groups and every 3 months thereafter.

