### Intervention group: MPVC and CAU

The intervention group will use MPVC consisting of two E-health tools: 1) the MSmonitor-Plus and 2) the video calling program: Beterdichtbij [22, 23].

MSmonitor-Plus allows patients to complete questionnaires, related to MS and MS-specific quality of life. By completing these every 3 months, a schematic overview can be created of the complaints so that care and treatment can be adjusted.

Beterdichtbij is a specific, secure video calling program that is used in Isala. With Beterdichtbij physical consultations can be replaced by video calling.

Patients in the intervention group receive CAU and MPVC. For MPVC, patients complete specific questionnaires four times a year, in consultation with their HCP, and they engage in video calls with their HCP at least twice a year. The patient’s answers (responses) are graphically displayed over time and recorded in the Electronic Patient File by the HCP. These responses with observation points from the HCP (during consultation) and tests (such as an MRI) inform treatment and care.

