The ICER is calculated as follows. ICER = (Ci - Cc) / (Ei - Ec), where Ci is the annual total cost of both study groups, Cc is the annual total cost of the control group (treatment by usual means), Ei is the effect at three-year follow-up for the intervention and control group, and Ec is the effect at the last follow-up for the control group (treatment by usual means).

The robustness of the ICER will be checked by non-parametric bootstrapping. Bootstrap simulations will also be conducted in order to quantify the uncertainty around the ICER, yielding information about the joint distribution of cost and effect differences. The bootstrapped cost-effectiveness ratios will be subsequently plotted in a cost-effectiveness plane, in which the vertical line reflects the difference in costs and the horizontal line reflects the difference in effectiveness. The choice of treatment depends on the maximum amount of money that society is prepared to pay for a gain in effectiveness, which is called the ceiling ratio. Therefore, the bootstrapped ICERs will also be depicted in a cost-effectiveness acceptability curve showing the probability that intervention and control groups are cost-effective using a range of ceiling ratios. In The Netherlands, a ceiling ratio between at € 20,000, € 50,000 and € 80,000 per QALY exists, depending on the burden of disease [60].

Additionally, to demonstrate the robustness of our base-case findings, a multi-way sensitivity analysis will be performed. In the sensitivity analysis uncertain factors of assumptions in the base case analysis will recalculated in order to assess whether the assumptions have influenced the incremental cost-effectiveness ratio (ICER), for example by varying cost-prices and volumes between minimum and maximum [61].

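### The lowest-price rule for uncertain unit costs is called conservative, but it is so only for resources that MPVC saves, not for those it adds

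*Protocol article*

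**What the plan says.** Under Cost evaluation outcomes, the protocol article builds costs bottom-up: "Costs will be calculated by multiplying volumes (resource use) with unit costs". Prices come from a national source: "For units costs we will used the Dutch cost guidelines". The programme's own costs are counted: "Intervention costs will include all the costs that will contribute to the development and administration of the MPVC and CAU", with training given as one example. For doubtful prices there is a single rule: "In case of uncertainty, we will use a conservative estimation (i.e. the lowest cost price". It is not limited to one arm or one cost category.

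Under Intervention group: MPVC and CAU, the programme comes on top of usual care ("Patients in the intervention group receive CAU and MPVC") but may also displace some of it ("With Beterdichtbij physical consultations can be replaced by video calling").

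Under Cost effectiveness analyses, the result is the ratio "ICER = (Ci - Cc) / (Ei - Ec"), judged against ceilings of EUR 20,000, 50,000 and 80,000 per QALY. A multi-way sensitivity analysis of base-case assumptions is planned, for example "by varying cost-prices and volumes between minimum and maximum". That section gives no other rule for base-case prices.

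**The concern.** In an economic evaluation, a conservative assumption is one that leans against the new programme. Whether a low price does so depends on which arm uses more of the resource. The rule ignores this, so its label does not describe what it does.

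What is at stake is how the base case is read. Someone told that doubtful prices were handled conservatively will take the base-case ICER as a cautious figure for MPVC. For the cost of the programme itself, it is the opposite. The base case also feeds the cost-effectiveness plane and the acceptability curve. The bootstrap resamples participants' data, not prices, so both displays carry the price choice unchanged.

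**Working it through.** The plan gives no price, volume or QALY figure here, so there is no stated figure to reproduce. The check is of direction first, then of possible size.

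**1. Direction.** Read Ci as the cost of the intervention arm. (The legend to the formula describes it as the cost of both groups, but the ratio makes sense only on this reading.) Let V be the volume of resources used only under MPVC, at price p, and S the volume of usual-care resources saved, at price q. With cost as volume times price:

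ΔC = Ci − Cc = p·V − q·S

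- Effect of p: ∂ΔC/∂p = V > 0. The lowest p lowers ΔC and favours MPVC.
- Effect of q: ∂ΔC/∂q = −S ≤ 0. The lowest q raises ΔC and works against MPVC whenever S > 0.

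V is positive by the plan's own account, since the intervention arm receives usual care plus the programme. S may be positive, since visits can be replaced.

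**2. Net effect.** Illustration with assumed inputs: V = 8 units per patient, both prices uncertain over EUR 50–100 (midpoint 75).

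| Visits saved, S | ΔC, lowest prices | ΔC, midpoints | Effect of the rule |
|---|---|---|---|
| 0 | 400 − 0 = 400 | 600 − 0 = 600 | −200, favours MPVC |
| 4 | 400 − 200 = 200 | 600 − 300 = 300 | −100, favours MPVC |
| 8 | 400 − 400 = 0 | 600 − 600 = 0 | none |
| 12 | 400 − 600 = −200 | 600 − 900 = −300 | +100, against MPVC |

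If only the programme's price is uncertain and 4 visits are saved at a fixed EUR 75, ΔC is 400 − 300 = 100 at the lowest price, 300 at the midpoint and 500 at the highest. If only the visit price is uncertain (programme price fixed at EUR 75, 4 visits saved), ΔC is 600 − 200 = 400 at the lowest visit price and 600 − 400 = 200 at the highest. The sign of the net effect thus depends on volumes and on which prices are uncertain. The document gives neither.

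**3. Size for the added items alone.** Assumptions: added cost EUR 500 per patient at mid-price (range 250–1,000); lowest price 30% below mid (range 20–50%); savings ignored.

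- Understatement: 500 × 0.30 = EUR 150. Range: 250 × 0.20 = 50 to 1,000 × 0.50 = 500.
- Per QALY at a gain of 0.01: 150/0.01 = EUR 15,000 (5,000–50,000).
- At 0.05: 150/0.05 = EUR 3,000 (1,000–10,000).
- At 0.10: 150/0.10 = EUR 1,500 (500–5,000).

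A statement that needs no assumed gain: EUR 150 is worth 150/20,000 = 0.0075 QALY at the lowest ceiling, 150/50,000 = 0.003 at the middle one and 150/80,000 ≈ 0.0019 at the highest.

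**4. What the sensitivity analysis does.** An item already priced at its minimum can only move upward. The range is shown, but the base case stays at its lower edge for every uncertain price.

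**The case against.** **The rule may work against MPVC overall.** It covers all cost categories in both arms. The plan hopes for fewer consultations and lower health and social costs, and for saved items the lowest price counts against the programme. This stands. A reader might infer that the base-case ICER is biased in favour of MPVC; the document does not support that, because the net sign is open. What remains is that an unconditional rule cannot be called conservative.

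**Uncertain prices need not be programme prices.** One might argue that standard visits have guideline prices, so doubt will fall mainly on the platform and its development. That is plausible but nowhere stated. The guideline source is named for unit costs in general, and resource use for the interventions is based on registered professional time, which may well have a reference price. The point should not rest on this inference.

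**The sentence follows the text on friction costs and may concern productivity only.** The order is as described, and the sentence does not mention the base case. But nothing restricts it, and the sentences that follow use the term cost prices generally. Even on the narrow reading, the lowest price is cautious only if MPVC reduces productivity losses, which the trial has yet to show.

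**The sensitivity analysis already handles it.** In part. It shows the effect of higher prices but changes neither the base case nor its label.

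**The amounts are hypothetical.** They are. A reader might infer that a modest price error would carry the ICER across the ceilings. That depends on a very small QALY gain. The document states no expected QALY difference; its hypothesis is improved quality of life, and its non-inferiority margin concerns the MSQOL-54.

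**Conclusion.** The concern holds in a limited form. The lowest-price rule is conservative for resources that MPVC saves and favourable to MPVC for resources that it adds. The direction for added items follows from the plan's own costing formula and needs no assumption beyond a positive volume of programme resources. The net effect on the ICER cannot be determined from the document.

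The euro amounts above are illustrations. They rest on an assumed programme cost, an assumed price spread and no savings, and per QALY they vary tenfold between gains of 0.01 and 0.10. The matter belongs to the economic evaluation and leaves the MSQOL-54 analysis untouched. Severity is minor to moderate: the existing sensitivity analysis softens it, but the base case rests on a rule that lacks the property claimed for it.

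**What to change.** Replace the sentence under Cost evaluation outcomes with wording such as:

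> Where a unit price is uncertain, the base case uses the guideline reference price or, if none exists, a central estimate of the plausible range, in both study groups. Lowest and highest prices are reserved for the sensitivity analysis, which includes one scenario unfavourable to MPVC: highest prices for items it adds and lowest prices for items it saves.

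Drop the word conservative. Settle the change before costs are compared between the arms.

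The cost is small: no new data, a documented range for each uncertain price, and one further scenario within a sensitivity analysis that is already planned. The base-case cost may turn out less favourable to MPVC than under the present rule.

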#### Process evaluation outcomes

The primary endpoint is the entire process of introducing MPCV over a 2-year period.

Process evaluation will be performed to assess whether MPVC was delivered in accordance with protocol, to examine the experiences and opinions of patients, caregivers and professionals regarding MPVC, and to determine to what extent MPVC has impacted adherence among patients. Process evaluation will be performed in accordance with the framework provided by Saunders et al [54]. This framework consists of a stepwise approach in which important characteristics for the process-evaluation plan are identified along seven basic components, i.e.: fidelity (quality), dose delivered (completeness), dose received (exposure), dose received (satisfaction), reach (participation rate), recruitment and context.

We will use a mixed method design in which both qualitative and quantitative data will be collected. The qualitative part will consist of observations during several group sessions over time. After each observation, a short interview will be held with the group leader(s) in which the group leader can reflect on his/her opinion regarding the session. During the last (sixth) group session of every MCI-group, a short evaluation form will be handed out to patients in which they will be asked to rate different aspects and themes of MPVC on a 7-point Likert scale. Furthermore, at the end of the study, focus groups will be held consisting of patients included in the study. The selection of participants will be based on maximal variation to get as many perspectives as possible. Participants will be selected based on age, gender, MS severity, cognition and effectiveness of the intervention (in order to compare patients in whom the intervention was successful versus unsuccessful). Focus groups will be conducted using a semi-structured questionnaire covering the topics identified in the framework provided by Saunders et al. [54].

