### MSmonitor-plus and video calling care (MPVC)

We designed a new multi-modal version of MS monitor, called MS monitor-Plus and Video calling Care (MPVC), a self-management and /education program with e-health interventions that combines more frequent use of specific questionnaires with video calling in treatment and self-management of MS patients.

In this study, we will use the digital self-management application MSmonitor, which is NEN7510 and ISO27001 certified and developed in 2009 for MS patients with a focus on online self-measurements [19–21]. MSmonitor has an educational program with e-health intervention. MSmonitor provides insight into disease symptoms, helps achieve personal goals, and aims to increase the patient’s input in shared decision-making. Thus, the patient and the HCP can work efficiently and effectively together to obtain the best possible treatment.

MSmonitor provides patients and HCP’s with qualitative disease-specific and general patient-reported outcomes. The scores are automatically calculated and displayed on a dashboard. Changes are visible at a glance [22].

We have designed a new multi-modal version of MSmonitor, MSmonitor-Plus.

The consultations consist of MSmonitor-Plus appointments. MSmonitor-Plus appointments (completion of the specific questionnaires by the MS patients with interpretation and assessment by the HCP) are scheduled every 3 months.

Each nurse specialist has his/her own MS patients for whom they perform the checks. The results from the MSmonitor-Plus are in the Electronic Patient File.

In MPVC consulting and feedback can be given to the patient via the video calling program Beterdichtbij®. Beterdichtbij is a medical video calling program that complies with the guidelines of the Doctors’ Federation KNMG and is also NEN7510:2017 and ISO 27001 certified (Beterdichtbij, Utrecht, The Netherlands) [23]. Beterdichtbij program uses Microsoft Teams, a video calling program, which is integrated into the Electronic Patient File. In this process, the patient goes from the virtual waiting room to the consulting room, where the image connection starts with the HCP [24].

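### Three process-evaluation instruments are tied to group sessions and group leaders that the described MPVC intervention does not contain

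*Protocol article*

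**What the plan says.** The Process evaluation outcomes section of the protocol article sets out a mixed-method evaluation with four named activities. On the first it says: "The qualitative part will consist of observations during several group sessions over time". The second is a short interview with the group leader or leaders after each observation. The third is a form on which patients rate aspects of MPVC on a 7-point scale: "During the last (sixth) group session of every MCI-group, a short evaluation form will be handed out to patients". The fourth is a set of patient focus groups at the end of the study.

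The intervention is described in two other places. The section headed Intervention group: MPVC and CAU states: "The intervention group will use MPVC consisting of two E-health tools: 1) the MSmonitor-Plus and 2) the video calling program: Beterdichtbij". The same section gives the yearly contact pattern: "patients complete specific questionnaires four times a year, in consultation with their HCP, and they engage in video calls with their HCP at least twice". The introductory section on MPVC says: "The consultations consist of MSmonitor-Plus appointments", and on who delivers them: "Each nurse specialist has his/her own MS patients for whom they perform the checks".

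**The concern.** The process evaluation is one of the three declared parts of the study. Its research questions ask whether MPVC was delivered as planned, what patients, informal caregivers and HCPs think of it, and whether it affected patients and shared decision-making. Three of the activities meant to inform these questions are attached to a group format with leaders and a sixth, final session. Nothing else in the article describes such a format. A field team following the text would have no session to observe, no leader to interview and no moment to hand out the form.

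This is not detail left to a fuller document. The article states a specific procedure, and that procedure does not fit the intervention the article itself describes.

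**Working it through.** No figure in the plan is in dispute, so the check sets the process-evaluation text against every other place where a group component would have to appear.

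1. **Components.** The Intervention group section names two tools, a questionnaire platform and a video-calling program. Neither is a group activity.
2. **Form of contact.** The introductory section on MPVC has one patient moving from a virtual waiting room into a consultation with the HCP. The sentence that consultations consist of MSmonitor-Plus appointments does not by itself say they are individual. The individual caseload of each nurse specialist and the patient-to-HCP wording for video calls do.
3. **Staff.** Study population(s) lists an investigator, a research nurse, a neurologist and a nurse specialist. There is no group leader.
4. **Recorded contacts.** Data collection methods has the investigator record, every 3 months, MSmonitor-Plus consultations, visits in person, video and telephone contacts, and dates of questionnaire completion. Group sessions are not on the list.
5. **Control arm.** The two care-as-usual sections describe face-to-face consultations, so the groups are not there either.
6. **Terminology.** MCI occurs only in the process-evaluation section and is missing from the abbreviation list.
7. **Could a group session be a loose term for a consultation?** The schedule does not support that reading:
   - MSmonitor-Plus rounds after baseline: 24 months / 3 months = 8 (9 with baseline).
   - Minimum video calls: 2 per year × 2 years = 4, with no fixed maximum.

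   Neither is a course that ends at a sixth session. A patient might happen to have six video calls, but the plan defines no such endpoint.

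Next, what each affected instrument supplies and what remains without it:

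| Information sought | Stated source tied to group sessions | Source that remains |
|---|---|---|
| Fidelity by direct observation | Session observations | None by observation; contact records and focus groups bear on fidelity indirectly |
| HCP experience | Group-leader interviews | None stated; the focus groups consist of patients |
| Patient ratings of MPVC itself | 7-point form | Focus groups (qualitative); the PTO is the hospital's satisfaction questionnaire, given in both arms and not described as MPVC-specific |
| Dose delivered and received | None | Contact moments and completion dates |
| General satisfaction | None | PTO at baseline, 12 and 24 months |

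Process evaluation analyses plans frequencies, means and medians for semi-quantitative data. The 7-point form is the evident input to these.

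Timing matters for any replacement. Inclusion ran from 27 April 2021 to 31 May 2022 (Results), and the article appeared on 12 November 2022. Patients included before about 12 November 2021 had then already passed 12 months. The earliest 24-month point was 27 April 2023, so month 24 still lay ahead for everyone.

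**The case against.** The strongest reply is that much of the process evaluation does not depend on group sessions. The contact log gives direct evidence on dose and on adherence to the planned schedule. The nurse specialist checks questionnaire completion at every 3-monthly appointment. The PTO measures satisfaction, and the focus groups use a semi-structured guide built on the same framework, so they reach fidelity and satisfaction as well. This stands. A reader might infer that the fidelity and experience questions would go wholly unanswered, or that most of the evaluation's data are lost; the article does not support either. The interviews also follow from the observations, so counting them as an independent lost source would inflate the loss.

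A second reply is that the full protocol is not shown. The article calls MPVC a self-management and education program without saying how the education is delivered, so a group element cannot be excluded outright. This also stands as a limit on wording. The supported statement is that the article describes no group sessions, not that none exist. It does not remove the conflict, because an undescribed group course would leave the two-tool definition and the contact list incomplete.

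A reader might further infer that the text was carried over from another, group-based programme. The undefined abbreviation makes that plausible, but the document does not confirm it, and the point does not need it.

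**Conclusion.** The point holds as an internal contradiction of limited reach. As the article stands, the observations, the interviews that follow them and the 7-point form have no occasion in the described intervention. Observed fidelity, HCP experience and MPVC-specific patient ratings are therefore left without a workable stated source. HCP experience is hit hardest, because the section names no other provider-side source.

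The conclusion assumes that the article's account of the intervention, the staff and the recorded contacts is complete. No estimate, error rate or sample size changes. It should be corrected, because it makes a stated part of the study impossible to carry out as written, but it does not threaten the trial's main conclusions.

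**What to change.** Reconcile Process evaluation outcomes with the intervention description and with the contact list in Data collection methods:

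- Tie the planned observations to a sample of MSmonitor-Plus appointments and video consultations.
- Replace the group-leader interviews with interviews of the nurse specialists and neurologists who deliver those contacts.
- Send the 7-point form through the eCRF to MPVC patients at 24 months, alongside the PTO. A 12-month form could not reach everyone, because some patients were already past that point when the article appeared.
- State that dose delivered and dose received come from the recorded contact moments and questionnaire completion dates.
- Remove or define the MCI abbreviation.

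If group sessions do exist, describe them instead as part of the intervention, including number, content and leader, and add them to the recorded contacts.

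The cost is a wording change, one short eCRF form and some rescheduled fieldwork for observations and staff interviews. The contact and completion data are already being collected.
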